#### Message Schedule

Messages will be delivered 3 times per week, beginning in the predelivery period and continuing until the child reaches 12 months of age. This schedule ensures continuous exposure to age-appropriate information during pregnancy and early infancy.

#### Application Onboarding

At enrollment, the RA will install the app on the smartphones of participants randomized to the intervention arm and provide a hands-on demonstration of its functionality to ensure correct initial use. To further optimize intervention adherence, participants will receive automated in-app notifications informing them of newly released content, along with reminder messages if content remains unaccessed for 48 hours. These prompts are intended to minimize missed exposure and sustain consistent engagement with the intervention over time.

#### Intervention Adherence Optimization

In addition, adherence optimization will be reinforced through active monitoring and follow-up. The RA will conduct fortnightly contacts to assess app performance, identify barriers to use, and provide tailored support to improve continued engagement, thereby strengthening intervention adherence throughout the study period. Technical troubleshooting will be supported by the Digital Health Resource Center team. At each follow-up visit, the RA will verify app functionality and reinstall the app if required.

#### User Engagement Metric

A set of engagement indicators will be derived from *MixPanel* mobile analytics [47], including video view counts, module completion status, time spent on each module, and frequency of app access. These metrics will provide an objective, time-stamped record of participant interaction with the intervention, enabling assessment of both the intensity and pattern of exposure over time.

#### Intervention Fidelity Assessment

The user engagement indicators will be used to assess intervention fidelity by evaluating the extent of participant exposure and adherence to the intervention as intended. Fidelity will be evaluated through cumulative exposure to scheduled content, the proportion of modules completed, and the average duration of interaction with intervention components. Based on predefined thresholds, participants will be categorized into fidelity groups as high (≥70% of scheduled content viewed and ≥70% of modules completed), moderate (40%‐69% of scheduled content viewed), and low (<40% of scheduled content viewed) fidelity [48]. These fidelity classifications will allow examination of dose-response relationships between intervention exposure and primary outcomes and will help interpret the effectiveness of the intervention in relation to varying levels of engagement.

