**Methods:**

This is a prospective, parallel-arm randomized controlled trial planned at a secondary care hospital in Karachi, Pakistan. The study will enroll 300 booked singleton pregnant women in the third trimester, who plan to stay in their respective areas for at least 1 year postdelivery, are registered for child immunization at the associated Family Health Center, own smartphones with internet access, are able to read Urdu, and provide consent. Participants in the intervention arm will receive the *Pehli Ghiza* mHealth app along with routine standard-of-care F2F counseling. The app will deliver context-specific educational content on breastfeeding and IYCFPs through short videos and messages sent 3 times per week, tailored to the stage of pregnancy and infant age. Participants in the control arm will receive only routine F2F counseling. The standard of care will be delivered at each follow-up visit, which is scheduled at birth, at 6, 10, and 14 weeks, and at 6, 9, and 12 months of the infant’s age. Data will be collected at enrollment and at each follow-up visit using structured questionnaires. Primary outcomes are EBF and the introduction of age-appropriate complementary feeding. Secondary outcomes include early initiation of breastfeeding, continued breastfeeding at 1 year, minimum dietary diversity, meal frequency, minimum acceptable diet, and child health outcomes. Analysis will follow the intention-to-treat principle to detect a 20% absolute improvement in primary outcomes between the intervention and control groups over time and to evaluate between-group differences in feeding practices. Compliance will be determined by the proportion of participants who complete the 6-month coaching program. Usability will be assessed based on features related to design, interface, content, coaching, perception, and personal benefit.

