### Study Participants

#### Inclusion Criteria

Inclusion criteria were as follows: women aged 18 years or older, at 36±1 weeks of gestation, with a singleton pregnancy without risk factors, registered for delivery at the study sites, planning to stay in their respective areas for at least 1 year postdelivery and to register for child immunization at associated Family Health Centers, owning smartphones with internet access, able to read Urdu, and providing consent for participation.

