### Outcome Measures

#### Outcome Assessment and Schedule

The outcome indicators are derived from WHO IYCF indicators [49,50]. Outcome data will be collected using structured interviewer-administered questionnaires and anthropometric assessments at predefined follow-up visits. The schedule of outcome measurements is presented in Table 2.

**Table 2. T2:** Schedule of enrollment, interventions, and assessments of participants as per SPIRIT (Standard Protocol Items: Recommendations for Interventional Trials).

Study steps	Baseline	Postallocation						
		Birth	6 wk	10 wk	14 wk	6 mo	9 mo	12 mo
Enrollment and allocation								
Eligibility screen	✓^a^							
Informed consent	✓							
Randomization	✓							
Allocated intervention								
mHealth^b^ coaching	mHealth coaching will occur continuously across the study period with the SoC^c^, not just at specific time points							
Face-to-face counseling	✓	✓	✓	✓	✓	✓	✓	✓
Participants characteristics								
Maternal	✓							
Infant		✓						
IYCF^d^ knowledge, attitude, and breastfeeding self-efficacy								
Baseline (at enrollment)	✓							
Midline (14th wk)					✓			
Endline (12th mo)								✓
Study outcome								
Early initiation of breastfeeding		✓						
Exclusive breastfeeding^e^			✓	✓	✓	✓^e^		
Continuation of breastfeeding at 1 y			✓	✓	✓	✓	✓	✓
Introduction of age-appropriate complementary feeding^e^						✓^e^	✓	
Minimum dietary diversity						✓	✓	✓
Minimum meal frequency						✓	✓	✓
Minimum acceptable diet						✓	✓	✓
Anthropometry		✓	✓	✓	✓	✓	✓	✓
Acute respiratory infection			✓	✓	✓	✓	✓	✓
Acute diarrhea			✓	✓	✓	✓	✓	✓
Visit to emergency room			✓	✓	✓	✓	✓	✓
Hospitalization			✓	✓	✓	✓	✓	✓
mHealth usability								
Assessment								✓

a ✓ indicates step conducted or outcome measured at the specific time point.

b mHealth: mobile health.

c SoC: standard of care.

d IYCF: infant and young child feeding.

e The 6-month assessments of exclusive breastfeeding and age-appropriate complementary feeding will serve as the primary outcome.

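### The fidelity classes leave some mothers unclassified, have no stated 6-month cut-off, and support only a descriptive dose-response comparison

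*Protocol article*

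**What the plan says.** The Intervention Fidelity Assessment section presents its cut-offs as predefined. It states that "participants will be categorized into fidelity groups as high (≥70% of scheduled content viewed and ≥70% of modules completed), moderate". The middle class then covers viewing from 40 to 69 per cent, and the bottom class covers anything under 40 per cent. The top class has two conditions; the other two use viewing alone.

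The exposure measure is cumulative: "Fidelity will be evaluated through cumulative exposure to scheduled content, the proportion of modules completed", together with average duration of interaction. No end date is given. The purpose is stated next: "These fidelity classifications will allow examination of dose-response relationships between intervention exposure and primary outcomes", and the classes are also to help interpret effectiveness by level of engagement.

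Three other places bear on the window:

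- Message Schedule: "Messages will be delivered 3 times per week, beginning in the predelivery period and continuing until the child reaches 12 months of age".
- Footnote to Table 2: "The 6-month assessments of exclusive breastfeeding and age-appropriate complementary feeding will serve as the primary outcome".
- Abstract, Methods: "Compliance will be determined by the proportion of participants who complete the 6-month coaching program".

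The Data Analysis Plan analyses all participants as randomised and does not use the fidelity classes.

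**The concern.** There are three weaknesses, all in the same secondary analysis.

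1. **Classes.** A set of predefined classes should place every app user in exactly one class. This set does not. The unplaced mothers lie at the upper boundary, which largely determines any gradient, and someone would have to place them after the data are in.

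2. **Window.** If exposure accumulates over everything scheduled to 12 months, the dose related to a 6-month outcome includes content that arrived too late to affect it. Mothers who used the app fully up to 6 months and then stopped would look only partly exposed. The programme length in the Abstract also disagrees with the delivery schedule.

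3. **Comparison.** Engagement arises after randomisation and is defined only in the app arm. Mothers who are keen to breastfeed may also open more content, and a mother who has stopped exclusive breastfeeding has less reason to open content about it. Either path could produce a gradient without any app effect. The section gives no caution on this, and the Strengths section credits the usage data with improving internal validity.

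**Working it through.** The plan gives no figure for this point, so there is none to reproduce.

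**Step 1. Do the classes cover everyone?** Let C be the percentage of scheduled content viewed and M the percentage of modules completed.

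- High: C ≥ 70 and M ≥ 70
- Moderate: 40 ≤ C ≤ 69
- Low: C < 40

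Two regions are left over:

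- C ≥ 70 with M < 70. Example: C = 80, M = 50.
- 69 < C < 70. With 168 scheduled messages (step 2), 116/168 = 69.05% and 117/168 = 69.64% fall here. Rounding to whole percentages would close this gap but not the first.

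The documents give no engagement distribution, so the size has to be assumed. C and M were simulated as normal, limited to 0–100%, with equal means of 50–70%, SD 20 points and correlation 0.5–0.9. About 4–17% of users fall in the first gap and 1–2% in the second.

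**Step 2. How much scheduled content comes after the outcome?** Inputs are 3 messages per week to 12 months (Message Schedule), enrolment of "women aged 18 years or older, at 36±1 weeks of gestation" (Inclusion Criteria), and primary outcomes at 6 months (Table 2). Assumptions are delivery at 40 weeks, hence w = 3 to 5 predelivery weeks; 6 months = 26 weeks and 12 months = 52 weeks; and messages as the unit of scheduled content.

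Total = 3 × (w + 52). After 6 months = 3 × 26 = 78.

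| w | Total | Up to 6 months | After 6 months | Share after |
|---|---|---|---|---|
| 3 | 165 | 87 | 78 | 47.3% |
| 4 | 168 | 90 | 78 | 46.4% |
| 5 | 171 | 93 | 78 | 45.6% |

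Effect on viewing percentages, with w = 4:

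- All content viewed up to 6 months, none later: 90/168 = 53.6%, moderate. Cut at 6 months: 100%.
- 70% viewed up to 6 months, none later: 0.70 × 90 = 63, and 63/168 = 37.5%, low. Cut at 6 months: 70%, which meets the viewing condition for high.
- 40 messages viewed up to 6 months, all viewed later: (40 + 78)/168 = 70.2%, which meets the viewing condition for high. Cut at 6 months: 40/90 = 44.4%, moderate.

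**Step 3. What gradient could appear if the app did nothing?** Exclusive breastfeeding in the app arm was set at 48%, the control rate in the Sample Size section. Engagement and outcome were given a latent normal correlation ρ, which is an assumption. Mothers were split into engagement thirds as a stand-in for the classes. A trend test at the 5% level was run on 150 × 0.80 = 120 mothers.

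| ρ | Low / middle / high third | High minus low | Trend test rejects |
|---|---|---|---|
| 0 | 48 / 48 / 48% | 0 points | 5% |
| 0.1 | 44 / 48 / 53% | 9 points | 12% |
| 0.2 | 39 / 48 / 57% | 18 points | 34% |
| 0.3 | 35 / 48 / 61% | 27 points | 66% |

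Differences are from unrounded rates. At ρ of 0.2 to 0.3 the spurious gradient is about the size of the 20-point effect for which the trial is powered.

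**The case against.** The first gap in the classes has no good answer. The rest can be contested.

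**Window.** A reader might infer that the trial will count app use after 6 months towards the dose for the 6-month outcomes. No sentence says so. The User Engagement Metric section describes time-stamped logs, so a cut at 6 months is available, and a condensed article may leave the window of a secondary analysis to the full plan. What stands is narrower. The article names a cumulative measure over scheduled content, runs that schedule to 12 months, relates it to 6-month outcomes and does not connect the three. The 6-month programme in the Abstract and the 12-month delivery also remain in conflict.

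**Causal claim.** A reader might infer that the plan offers the gradient as proof that the app works. It does not: it speaks of examining dose-response and of helping interpretation, and efficacy rests on the randomised comparison. This objection stands. The point is a missing caution, not a false claim.

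**Size.** A reader might conclude that engaged mothers would produce a gradient in any event. That goes too far. The correlation appears nowhere in the documents; at zero there is no gradient, and at 0.1 it is about 9 points. The correct word is could.

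**Remedy.** Truncation at 6 months does not cure reverse causation. A mother who stops exclusive breastfeeding at 8 weeks may view less from then until 6 months. This also stands and limits what the fix can claim.

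**Conclusion.** The point holds as a correction to a secondary analysis. From the text alone it is certain that the classes are not exhaustive. How many mothers are affected is not known; 4–17% depends on the assumed distributions.

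The window mismatch follows from a literal reading: 46–47% of scheduled messages come after the primary outcomes, given delivery at 40 weeks and messages as the unit. The 6- and 12-month programme lengths disagree within the article and must be reconciled.

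The dose-response comparison is non-randomised. Without any app effect it could show 0 to about 27 points for an assumed correlation of 0 to 0.3.

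None of this touches the intention-to-treat comparison, which does not use the classes. It would be wrong to infer that the trial's primary result is at risk.

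**What to change.** 1. Define moderate as at least 40% of content viewed and not meeting the definition of high. This closes both gaps.
2. For analyses against the primary outcomes, compute viewing and module completion only from content scheduled before the 6-month assessment.
3. Reconcile the 6-month programme in the compliance definition with delivery to 12 months.
4. Label the gradient descriptive and non-causal, and state that the 6-month cut does not remove reverse causation within the first 6 months.
5. If an effect in users is wanted, use randomisation as the instrument, with any use or percent viewed as the exposure. Do not use the high class as a binary exposure: that assumes no benefit in moderate and low users, and the estimate is inflated if they do benefit. With percent viewed, state the linear-dose assumption. State the no-contamination assumption as well, because the Intervention Access Control section provides for unauthorised access and the Limitation section accepts that information may be shared between arms.

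**Cost.** Items 1 to 4 are wording and use data already logged. Item 5 is one extra analysis, with a wider interval than the naive gradient. The timing allows it: recruitment began on February 2, 2026, and the latest date the article reports is May 18, 2026. That is 105 days, or 15 weeks, so no infant born after enrolment could yet have reached 26 weeks.

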#### Technical Architecture

*Pehli Ghiza* was developed with support from the Digital Health Resource Center of the Aga Khan Development Network. The app development stack includes the Flutter software development kit (SDK; version 3.38) for cross-platform, high-performance development; the Dart SDK bundled with Flutter 3.38 programming language; the Android SDK latest stable (API level 35) for Android platform tools and libraries, Android Studio latest stable release for integrated development environment and Gradle (version 8.5) to build automation, dependency management, and optimized Android builds. It is available on the Android and iOS platforms via the Google Play Store and Apple App Store. The software architecture follows a modular, service-oriented design, with clearly defined functional components for user authentication, content management, notification delivery, analytics tracking, and data synchronization. All intervention content will be finalized and frozen prior to participant enrollment. No modifications, additions, or removals of educational content will be made during the 12-month trial period.

#### App Version Control

A single, version-controlled release of *Pehli Ghiza* will be used for all intervention participants to ensure consistency of exposure. Any updates during the trial, if required, will be limited strictly to technical maintenance (eg, bug fixes or compatibility updates) that does not alter content, messaging, or functionality. All such changes will be documented with version numbers, timestamps, and change logs. This approach is adopted to minimize the risk of confounding due to midtrial intervention modifications.

#### Intervention Access Control

Although *Pehli Ghiza* is publicly available, access will be restricted through study-specific onboarding, registration, and backend activation, provided only to participants randomized to the intervention arm to mitigate contamination. The control group will not be able to access the app, as participants will not be provided with login credentials. Further, recruitment and follow-up procedures for both arms will be conducted separately to minimize cross-arm information exchange. App usage logs will be monitored to detect unauthorized access, and any crossover will be documented and addressed through intention-to-treat and sensitivity analyses.

### Control

#### Standard-of-Care F2F Counseling

Participants in both the control and intervention arms will receive F2F counseling by the RA at each follow-up visit as part of routine standard-of-care. To ensure consistency across study arms and follow-up visits, the RA will provide counseling using the AKUH patient education booklet (Figure 4) as a standardized counseling script. The booklet includes information on maternal nutrition, breastfeeding, IYCFPs, child health, growth, and immunization. Each counseling session will be approximately 20 minutes in duration and will not include additional reinforcement beyond standard service delivery.

#### Counseling Standardization and Fidelity Monitoring

The RA will undergo standardized training sessions for adherence to uniform counseling procedures and scripts. This will minimize variation in counseling content, delivery, and interaction across participants. To further ensure fidelity, periodic supervisory reviews and checklist-based monitoring of counseling sessions will be conducted throughout the study.

**Figure 4. F4:**
[figure not shown]
Standard of care is a patient information booklet that provides general information about child development, nutrition, growth, and vaccination record.

### Outcome Measures

#### Outcome Assessment and Schedule

The outcome indicators are derived from WHO IYCF indicators [49,50]. Outcome data will be collected using structured interviewer-administered questionnaires and anthropometric assessments at predefined follow-up visits. The schedule of outcome measurements is presented in Table 2.

**Table 2. T2:** Schedule of enrollment, interventions, and assessments of participants as per SPIRIT (Standard Protocol Items: Recommendations for Interventional Trials).

Study steps	Baseline	Postallocation						
		Birth	6 wk	10 wk	14 wk	6 mo	9 mo	12 mo
Enrollment and allocation								
Eligibility screen	✓^a^							
Informed consent	✓							
Randomization	✓							
Allocated intervention								
mHealth^b^ coaching	mHealth coaching will occur continuously across the study period with the SoC^c^, not just at specific time points							
Face-to-face counseling	✓	✓	✓	✓	✓	✓	✓	✓
Participants characteristics								
Maternal	✓							
Infant		✓						
IYCF^d^ knowledge, attitude, and breastfeeding self-efficacy								
Baseline (at enrollment)	✓							
Midline (14th wk)					✓			
Endline (12th mo)								✓
Study outcome								
Early initiation of breastfeeding		✓						
Exclusive breastfeeding^e^			✓	✓	✓	✓^e^		
Continuation of breastfeeding at 1 y			✓	✓	✓	✓	✓	✓
Introduction of age-appropriate complementary feeding^e^						✓^e^	✓	
Minimum dietary diversity						✓	✓	✓
Minimum meal frequency						✓	✓	✓
Minimum acceptable diet						✓	✓	✓
Anthropometry		✓	✓	✓	✓	✓	✓	✓
Acute respiratory infection			✓	✓	✓	✓	✓	✓
Acute diarrhea			✓	✓	✓	✓	✓	✓
Visit to emergency room			✓	✓	✓	✓	✓	✓
Hospitalization			✓	✓	✓	✓	✓	✓
mHealth usability								
Assessment								✓

a ✓ indicates step conducted or outcome measured at the specific time point.

b mHealth: mobile health.

c SoC: standard of care.

d IYCF: infant and young child feeding.

e The 6-month assessments of exclusive breastfeeding and age-appropriate complementary feeding will serve as the primary outcome.

#### Primary Outcomes

The primary end points of the study are (1) EBF at 6 months of infant age and (2) introduction of AACF [49,50] at 6 months of infant age.

In addition, EBF will also be assessed at the 6th, 10th, and 14th weeks, while CF practices will also be assessed at 9 months of infant age. The repeated assessments at additional time points will be used for longitudinal analyses to evaluate trends and sustainability of feeding practices over time. Operational definitions of the primary outcome measures are provided in Table 3.

**Table 3. T3:** Operational definitions of primary and secondary outcome measures.

Outcome	Operational definitions
Primary outcomes [49,50]	
Exclusive breastfeeding	Proportion of infants who are fed exclusively with breast milk up to 6 months of age
Introduction of age-appropriate complementary feeding	Proportion of infants who are introduced to solid, semisolid, or soft foods at 6 mos of age
Secondary outcomes	
Infant and young child feeding practices [49,50]	
Early initiation of breastfeeding	Proportion of children put to the breast within 1 hour of birth
Minimum dietary diversity	Proportion of children 6‐12 months of age who receive food from 4 or more food groups
Minimum meal frequency	Average number of daily meals for children 6‐12 months of age, who receive solid, semisolid, or soft foods
Minimum acceptable diet	Composite variable based on meal frequency and dietary diversity
Mean duration of breastfeeding	Average duration an infant is breastfeeding for 12 months
Continued breastfeeding at 1 y	Proportion of children 12 months of age who are still on breast milk
Child health	
ARI^a^	Short, rapid breathing that is chest-related and/or difficult breathing that is chest-related. Percentage of children up to 1 year of age with symptoms of ARI at any time in the last 2 weeks preceding the follow-up
Acute diarrhea	Passage of 3 or more loose or liquid stools per day (or more frequent passage than is normal for the individual). Percentage of children up to 1 year of age with symptoms of diarrhea at any time in the last 2 weeks preceding follow-up
Visit to the emergency room	Infant brought to the emergency room for management of any acute illness in past 2 weeks.
Hospitalization	Infant admitted to the hospital for diagnosis or management of any acute illness in past 2 weeks.
Stunting (height-for-age) [51]	Children whose height-for-age *z* score is below −2 SD from the median of the reference population used in the WHO^b^ Child Growth Standards [41]
Wasting (weight-for-height) [51]	Children whose weight-for-height *z* score is below −2 SD from the median of the reference population used in the WHO Child Growth Standards [41]
Overweight (weight-for-height) [51]	Children whose weight-for-height *z* score is more than 2 SD above the median of the reference population used in the WHO Child Growth Standards [41]
Underweight (weight-for-age) [51]	Children whose weight-for-age *z* score is below (−2 SD) from the median of the reference population used in the WHO Child Growth Standards
Breastfeeding self-efficacy [52]	A standard 14-item tool adapted and translated into Urdu language to determine self-efficacy in breastfeeding, rated on a 5-point Likert scale
mHealth^c^ usability [53]	A questionnaire to assess experience of mHealth application based on 6 domains: design, interface, content, coaching, perception, and personal benefit, rated on a 5-point Likert scale

a ARI: acute respiratory infection.

b WHO: World Health Organization.

c mHealth: mobile health.

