Despite modest progress, significant gaps persist in Pakistan’s infant and young child feeding (IYCF) indicators. The recent National Nutritional Survey reported improvements in EIBF from 40% (2011) [10] to 45% (2018) [3]; yet, nearly 40% of neonates continue to receive prelacteal feeds [3], undermining the benefits of colostrum feeding. Further, a nonlinear trend was found in EBF, decreasing from 50% (2001) [3] to 37.7% (2011) [10] before rising to 48% (2018) [3], reflecting inconsistent policies and nonsustainable interventions. The decline in EBF was particularly evident at 3 months of infant age, dropping from 84% to 70% [11], reportedly due to inadequate maternal knowledge about EBF and its associated benefits [12]. The continued breastfeeding practice at 1 year also declined from 77.3% (2011) [10] to 68.4% (2018) [3], with only 40.1% of children aged 0 to 23 months receiving age-appropriate breastfeeding [3]. This means that while initial breastfeeding practices may be improving, their maintenance and adherence remain inadequate and challenging. Further, the complementary feeding (CF) indicators were even more concerning. Only 36% of children aged 6‐8 months receive timely CF; minimum dietary diversity (MDD) is achieved by 14%, minimum meal frequency (MMF) by 18%, and a mere 3.6% of children meet the minimum acceptable diet (MAD) criteria [3], a composite indicator reflecting both meal frequency and diversity. These significant deficiencies impair infant physical growth, immunity, and cognitive development.

This alarming situation has not improved much, as a recent study conducted in rural Sindh Province reported that <10% of infants were EBF, with a significant proportion identified as wasted (14.7%), stunted (36.7%), and underweight (38.5%) at birth [13]. The study also found a significant association of early initiation of CF or breast milk alternatives before 4 months and increased odds of wasting by 6 months of age (adjusted odds ratio 4.14, 95% CI 1.95-8.77; *P*<.001) [13]. This further reflects persistent gaps in early child nutrition, which are the result of a complex interplay of inadequate maternal knowledge, sociocultural norms and myths, and insufficient nutritional counseling at health system touchpoints [14-16].

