### Follow-Up

Outcome assessments are aligned with the national Expanded Programme on Immunization schedule to maximize participant adherence. These will be collected at birth; at the 6th, 10th, and 14th weeks; and at the 6th, 9th, and 12th months of infant age by the RA. At each follow-up visit, participants in both study arms will receive F2F counseling. Follow-up windows of ±2 weeks will be permitted to accommodate participant availability and logistical constraints. Phone call reminders will be given prior to their appointments, with the option to reschedule, where needed. When in-person visits would not be feasible, counseling and outcome data will be collected through telephone follow-up or during subsequent health facility visits to minimize loss to follow-up.

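### The 6-month visit may fall two weeks early, and an infant seen before 6 months cannot meet both primary outcomes, so correct feeding is scored as a complementary-feeding failure

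*Protocol article*

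**What the plan says.** Primary Outcomes sets both endpoints at 6 months of infant age: "The primary end points of the study are (1) EBF at 6 months of infant age and (2) introduction of AACF", the latter at the same age. Footnote e of Table 2 ties them to one visit: "The 6-month assessments of exclusive breastfeeding and age-appropriate complementary feeding will serve as the primary outcome".

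Table 3 gives the definitions:
- EBF: "Proportion of infants who are fed exclusively with breast milk up to 6 months of age".
- AACF: "Proportion of infants who are introduced to solid, semisolid, or soft foods at 6 mos of age".

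The Follow-Up section states, for all follow-up visits: "Follow-up windows of ±2 weeks will be permitted to accommodate participant availability and logistical constraints". It makes no exception for the 6-month visit.

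A later reading exists ("CF practices will also be assessed at 9 months of infant age"), but it serves the longitudinal analyses and not the primary endpoint. The Introduction describes timely complementary feeding over a band of ages ("Only 36% of children aged 6‐8 months receive timely CF"). Table 3 does not carry that band over.

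Sample Size assumes control rates of 48% (EBF) and 50% (AACF) and a 20-point absolute improvement, which gives intervention-arm rates of 68% and 70%.

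**The concern.** The app advises breast milk alone for six months and added foods from 6 months (Table 1). The two outcomes are meant to capture two consecutive steps of that advice, the second starting when the first ends. A visit up to two weeks before 6 months sees only the first step. At such a visit the outcomes exclude each other, and the better the mother complies, the more surely she fails AACF.

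The AACF wording adds a second gap. It gives no age range and does not plainly say that solids begun at, say, 4 months are a failure. An infant with early solids has been introduced to them by the time of the visit and might be scored a success. At stake is what one of the two primary endpoints measures: part of it would reflect the date of the visit, and possibly early solids, rather than timely introduction.

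**Working it through.** **1. The plan's sample size.** Inputs from Sample Size: two-sided 5%, 80% power, 1:1, 20% loss. For AACF, n = [1.96·√(2·0.60·0.40) + 0.8416·√(0.50·0.50 + 0.70·0.30)]² / 0.20² = 93 per arm. Then 93/0.8 gives 117, or 234 in total (258 with continuity correction). EBF at 48% against 68% gives 95, then 119, or 238 in total (264 with correction). The stated 300 is not reproduced but exceeds all of these, and it is not part of this point. With 150 × 0.8 = 120 evaluable per arm, power is 89.0% for AACF and 88.6% for EBF.

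**2. Scoring by the stated definitions.**

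| Infant | EBF | AACF |
|---|---|---|
| Seen before 6 months, breast milk only so far | not broken | not met |
| Seen before 6 months, solids already given | broken | unclear: met if early solids count |
| Seen before 6 months, other fluids but no solids | broken | not met |
| Seen after 6 months, breast milk only to 6 months, then solids | met | met |

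No infant seen early can meet both. This needs no assumed figure.

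**3. What the planned rates require.** The share meeting both outcomes is at least 0.68 + 0.70 − 1 = 0.38. So at least 38% of intervention infants must meet both, and all of them must be seen at or after 6 months. If a share f is seen early, the two rates sum to at most f·1 + (1 − f)·2 = 2 − f. The planned sum of 1.38 therefore stays possible up to f = 0.62. The targets are constrained but not impossible.

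**4. Early solids do not count (illustration).** The documents do not give f; assume 0 to 50%, equal in both arms. Early-seen infants score 0, and the rest follow 50% and 70%. Power = Φ{[d − 1.96·√(2p̄(1 − p̄)/n)] / √([p₁(1 − p₁) + p₂(1 − p₂)]/n)}, n = 120.

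| f | Control | Intervention | Power |
|---|---|---|---|
| 0 | 50.0% | 70.0% | 89% |
| 10% | 45.0% | 63.0% | 80% |
| 25% | 37.5% | 52.5% | 65% |
| 50% | 25.0% | 35.0% | 39% |

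For f = 25%: (0.15 − 1.96 × 0.0642)/0.0635 = 0.38, and Φ(0.38) = 0.65.

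**5. Early solids count (illustration, upper bound).** Take every EBF failure as solids. Among early-seen infants AACF is then 1 − EBF: 52% in control and 32% in intervention, a difference of −20 points. Overall the difference is 20(1 − f) − 20f points: 16, 10 and 0 at f = 10%, 25% and 50%. Power is 71%, 34% and 2.5%.

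**6. When the sign can turn (illustration).** Assume visits uniform over ±2 weeks, EBF 48% against 68%, 90% of EBF mothers starting solids uniformly in the two weeks after 6 months, and a share e of the other infants starting early and having begun by the visit. Ignore later starters. An EBF infant is scored AACF with probability 0.90 × ½ × ½ = 0.225.
- Early solids count: the difference is 0.20 × (0.225 − e), so −1.5, −5.5 and −9.5 points for e = 30%, 50% and 70%.
- Early solids do not count: it is 0.20 × 0.225 = +4.5 points.

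**The case against.** The article is condensed. The questionnaire may ask the age at first solids, and the Follow-Up section allows collection by telephone or at a later visit. Both are fair, but the second applies when an in-person visit is not feasible and sets no rule for a visit made early. The article itself fixes the definitions, the time point and the window, and as written these do not fit together.

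Four stronger readings are tempting, and the documents do not support them.
- **A late visit also spoils EBF, because a correctly fed infant has started solids by then.** Table 3 defines EBF as feeding up to 6 months, not status on the visit day. Solids begun at 6 months do not break it.
- **The app will look harmful on AACF.** Step 6 shows a negative difference only if solids before 6 months count as success. Table 3 does not say that they do, and the name of the outcome speaks against it. If they do not count, the effect is diluted, not reversed.
- **Visit timing will differ between arms.** Schedule, reminders and fortnightly contact are planned alike for both arms. Nothing stated suggests a difference.
- **Half the infants will be seen early.** No visit-age distribution is given. At 10% seen early and scored 0, power is still 80%.

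**Conclusion.** The point holds for infants seen before 6 months. Under the stated definitions and window they cannot meet both primary outcomes, and a correctly fed one is scored an AACF failure. That follows from the text alone. Whether early solids count as AACF is left open, and the answer decides between dilution and a possible change of sign.

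The size cannot be fixed from the documents. It depends on the share seen early and on how early solids are scored; the power figures are illustrations over an assumed 0 to 50%, not forecasts. EBF as defined is not threatened by a late visit.

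The definition of a primary endpoint should be settled before data are read against it, and there was still time at the last reported status. Recruitment began on 2 February 2026 at 36±1 weeks. Even a birth on that day puts the earliest permitted 6-month visit, at about 24 weeks of age, near 20 July 2026, after the May 2026 recruitment reports.

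**What to change.** Record at each visit the infant's age at first other food or fluid and at first solids, and derive both primaries from these ages.
- **EBF:** nothing other than breast milk before 6 completed months, even if solids have begun by a later visit.
- **AACF:** first solids within a stated age band that starts at 6 completed months, with earlier introduction counted as failure.
- **Reading rule:** do not read AACF before the infant has reached 6 months and the band has closed. Complete an early visit at a later fortnightly contact or at the planned 9-month visit.

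The 6–8 month band in the Introduction, read at 9 months, is one option. A shorter band would also cure the defect.

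Restate the AACF control rate and power for the chosen band, without assuming that 300 still suffices. If the Introduction's 36% were the control rate and 20 points the effect, power at 120 per arm would be 0.88. But suppose, as in step 6, that a share e of non-EBF infants start early and all others start within the band. The rates are then 0.48 + 0.52(1 − e) and 0.68 + 0.32(1 − e): about 84% against 90%, 74% against 84% and 64% against 78% for e = 30%, 50% and 70%. Power is about 28%, 48% and 67%.

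Cost: two questionnaire items, revised outcome wording, a somewhat later AACF reading and a restated control rate. No new visit is needed.
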